#### Secondary Outcomes

Secondary outcome measures will be as follows:

Statistical evaluation of intraindividual differences in the VISA-A score and the Pain Disability Index (PDI), including all subscales, between values at baseline and weeks 4, 12, 26, and 52 after verum therapy compared to control.Pain on exertion after standing on one leg for 30 seconds, using the 11-point NRS: statistical evaluation of intraindividual differences between values at the beginning of treatment and before each therapy session and at weeks 4, 12, 26, and 52 after verum therapy compared to control.Average pain on average exertion in the last week, using the 11-point NRS: statistical evaluation of intraindividual differences between values at therapy start and before each therapy session and at weeks 4, 12, 26, and 52 after verum therapy compared to control.Return to exercise: statistical evaluation of intraindividual differences between values at baseline and at weeks 4, 12, 26, and 52 after verum therapy compared to control.Treatment response: statistical evaluation of verum therapy compared to control.Use of emergency medication (eg, the NSAID acetaminophen) within 1 week: statistical evaluation of intraindividual differences between values at baseline and at weeks 4, 12, 26, and 52 after verum therapy compared to control.

### Safety Evaluation Criteria

Safety evaluation criteria will be as follows:

Listing by month of treatment of adverse events (AEs), adverse reactions (ARs), serious AEs (SAEs), and serious ARs (SARs) stratified by organ classes and events: total sum, total AEs and ARs, total SAEs and SARs, total AEs and SAEs, and total ARs and SARs will be formed.Total listing of AEs, ARs, SAEs, and SARs, including suspected unexpected SARs, stratified by participant and organ classes and events: formed as the total sum, sum of AEs and ARs, sum of SAEs and SARs, sum of AEs and SAEs, and sum of ARs and SARs.Total listing of AEs, ARs, SAEs, and SARs stratified by organ class and severity (ie, intensity): formed as the total, total AEs and ARs, total SAEs and SARs, total AEs and SAEs, and total ARs and SARs.Listing of reasons for study exclusion (ie, violation of inclusion and exclusion criteria) with the duration of study participation to date.Calculation of the probability of occurrence of the respective number of AEs that occurred.

### Sample Size

The sample size is calculated on the basis of the primary outcome, taking into account a clinically relevant effect size between verum and control.

In this study, the treatment effect is considered clinically relevant if the effect size between study arms is at least Δ/σ = 0.75.

To demonstrate a significant treatment effect in the primary statistical analysis with 80% power using a 2-sided Wilcoxon-Mann-Whitney test at the *α*=.05 level, a sample size of 62 participants in total is needed, with 31 participants per intervention group.

The allocation ratio is 1 (verum) to 1 (control). Assuming a dropout rate of 15%, a total of 72 participants should be included in the study.

### Statistical Analysis

Statistical evaluation will generally be carried out using descriptive methods in the form of frequency tables and statistical parameters, such as means, SDs, and quantiles. As graphical procedures, bar charts will be created for qualitative data, and box-and-whisker plots will be created for quantitative data. In addition, inferential statistical analyses will be performed using appropriate significance tests and CIs. Missing values will not be replaced.

The primary statistical evaluation will be performed with a 2-sided Wilcoxon-Mann-Whitney test at the global significance level of *α*=.05; the results will be interpreted in a confirmatory sense.

The evaluation of the secondary evaluation criteria of efficacy will be performed with adequate 2-sided tests. Here, local levels (local level *α*=.05) will be controlled instead of the global significance level, and no adjustment will be made for multiple testing. *P* values of the secondary evaluation criteria will be interpreted descriptively only.

The safety evaluation criteria will be evaluated exploratively. In the exploratory evaluation of the safety criteria, adjustment for multiple testing would be counterproductive and will, therefore, not be performed.

For the primary target criterion, the following 2-sided test problem will be set up:

H_0_: *d*=0 versus H_1_: *d*≠0

where *d* indicates the effect size between intervention groups.

The null hypothesis is as follows: in the statistical evaluation of intraindividual differences between scores at start of treatment and at week 12, there will be no difference in the VISA-A score for symptom assessment between verum and control.

The research hypothesis is as follows: in the statistical evaluation of intraindividual differences between values at start of treatment and at week 12, there will be a difference in the VISA-A score for the assessment of symptomatology between verum and control.

For the secondary outcome of efficacy, corresponding 2-sided test problems will be set up and solved.

The evaluation of the primary and secondary outcomes will be performed according to the intention-to-treat (ITT) principle. The respective collective includes all participants included in the study, regardless of possible protocol violations (eg, study discontinuations or premature discontinuation of intervention). In addition to the ITT analyses, sensitivity analyses will be performed according to the per-protocol principle. Relevant protocol violations leading to exclusion from the per-protocol collective will be defined in the statistical analysis plan. The statistical analysis plan will be prepared in a blinded review without knowledge of the target criteria.

The safety evaluation criteria will be evaluated using the as-treated principle. That is, all participants who participated in the study and received at least one dose of the study intervention (ie, safety collective) will be included.

Subgroup analysis will only be done exploratively, as previous studies have shown that, for example, gender appears not to be a risk factor for AT [20].

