### Outcome Measures

#### Primary Outcome

The VISA–Achilles questionnaire (VISA-A) score [18] will be used as the primary outcome measure. Intraindividual differences between values at baseline and values 12 weeks after initial treatment with verum therapy compared to control will be evaluated. The VISA-A questionnaire is an index of the severity of a clinically diagnosed condition (ie, AT). It contains eight questions on three domains of pain, function, and activity. Scores are summed to a total with a maximum of 100. In this study, the German adaptation (VISA-A-G) will be used. The VISA-A-G questionnaire was tested for reliability, validity, and internal consistency [19].

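### The primary Wilcoxon-Mann-Whitney test on VISA-A change is valid and powered as stated, but adjusting for the baseline VISA-A already collected would gain precision, by an amount the article does not let us fix

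*Protocol article*

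**What the plan says.** The Primary Outcome section defines the endpoint on the VISA-A score: "Intraindividual differences between values at baseline and values 12 weeks after initial treatment with verum therapy compared to control will be evaluated". The Statistical Analysis section fixes the confirmatory method: "The primary statistical evaluation will be performed with a 2-sided Wilcoxon-Mann-Whitney test at the global significance level of" .05. The null hypothesis is also framed on change: "in the statistical evaluation of intraindividual differences between scores at start of treatment and at week 12, there will be no difference" in VISA-A between the arms. It is written formally as d=0, where d "indicates the effect size between intervention groups".

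The Sample Size section uses the same test. It states that "the treatment effect is considered clinically relevant if the effect size between study arms is at least Δ/σ = 0.75". The calculation is made "with 80% power using a 2-sided Wilcoxon-Mann-Whitney test at the *α*=.05 level", and the Sample Size section gives its result in these words: "a sample size of 62 participants in total is needed, with 31 participants per intervention group". With 15% dropout the total becomes 72.

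No covariate is named for the primary comparison. The Study Design section has primary outcome data collected at baseline. The Randomization section stratifies by study site only. The only sensitivity analysis named is per-protocol, and what is explicitly left to the SAP is the list of violations that define the per-protocol set.

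**The concern.** Subtracting the baseline removes exactly one point of outcome for each point of baseline. If the true regression slope of week-12 VISA-A on baseline is below 1, this over-corrects: participants who start low tend to show larger changes whatever arm they are in. Two things follow.

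- The change score carries variance that a fitted slope would remove.
- A chance difference between arms in baseline VISA-A passes into the treatment comparison. Randomization balances site but not baseline VISA-A, and with 31 per arm moderate imbalances are ordinary.

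The plan is sized at 80% power for a large standardized effect, so precision left unused matters. In addition, a rank-test p-value does not say how many VISA-A points separate the arms, while the relevance threshold is set on a standardized mean difference.

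**Working it through.** **Inputs from the article:** two-sided Wilcoxon-Mann-Whitney test, alpha 0.05, power 80%, Δ/σ = 0.75, 31 evaluable per arm, 1:1 allocation. **Assumed, because the article does not give them:** the correlation rho between baseline and week-12 VISA-A, and k = SD at baseline / SD at week 12. σ is read as the SD of the change score, since the endpoint is a change.

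**1. The plan's own figure.** A two-sample t-test with d = 0.75 needs 28.9 per arm. Dividing by 3/π, the efficiency of the rank test relative to the t-test under normality, gives 28.9 × π/3 = 30.3, hence 31 per arm and 62 in total. The stated figure reproduces. Approximate power at 31 per arm is 0.81, and simulation gives about 0.80.

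**2. Variance of the two estimators.** With the week-12 SD set to 1:

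- Change score: 1 + k² − 2·rho·k
- ANCOVA: 1 − rho²
- Ratio ANCOVA/change: (1 − rho²)/(1 + k² − 2·rho·k)

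The difference change minus ANCOVA is (k − rho)², which is never negative. In large samples adjustment therefore cannot lose precision. In finite samples it costs one degree of freedom. With k = 1 the ratio is (1 + rho)/2, so the reduction is (1 − rho)/2.

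| k | rho 0.3 | rho 0.5 | rho 0.7 |
|---|---|---|---|
| 1 | 35% | 25% | 15% |
| 0.85 | 25% | 14% | 4% |
| 0.7 | 15% | 5% | 0% |

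With k = 1, rho 0.8 gives 10% and rho 0.9 gives 5%. Worked case, k = 0.7 and rho = 0.3: (1 − 0.09)/(1 + 0.49 − 0.42) = 0.91/1.07 = 0.85, a 15% reduction. At k = 0.7 and rho = 0.7 the true slope is rho/k = 1, so the change score is already optimal and the reduction is zero.

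**3. Power at 31 per arm, effect 0.75 SD of change.** Simulated with normal data:

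| k | rho | Planned test | ANCOVA |
|---|---|---|---|
| 1 | 0.3 | 0.80 | 0.95 |
| 1 | 0.5 | 0.80 | 0.91 |
| 1 | 0.7 | 0.81 | 0.88 |
| 0.7 | 0.3 | 0.80 | 0.88 |
| 0.7 | 0.5 | 0.81 | 0.85 |
| 0.7 | 0.7 | 0.80 | 0.82 (0.83 by formula) |

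Null rejection was near 5% for both methods. In the last row the small advantage comes from using a t-type test instead of a rank test on normal data, not from baseline adjustment.

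**4. Chance imbalance.** The standard error of the baseline difference is √(2/31) = 0.254 baseline SDs. An imbalance of one standard error shifts the change contrast by (1 − rho) × 0.254 SD when k = 1. Dividing by the SD of change, √(2(1 − rho)), gives 0.15, 0.13 and 0.10 SDs of change at rho 0.3, 0.5 and 0.7. Relative to the target of 0.75 that is 20%, 17% and 13%. With k = 0.7 the corresponding shifts are 0.10, 0.06 and 0.

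**The case against.** The strongest reply is that nothing in the plan is wrong. Endpoint, hypotheses, test and sample size agree with one another, type I error is protected by randomization, and the intended power is reached. All of this stands.

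A reader might infer that the plan wastes 15-35% of its information. The article does not support that as a fact. The range needs both rho between 0.3 and 0.7 and equal SDs, and neither is given. Equal SDs are open to doubt: eligibility limits pain intensity and duration at entry, which may narrow baseline VISA-A, while nothing limits week 12. At k = 0.7 the gain can vanish. It is also inexact to say that the plan ignores the baseline, because the change score uses it with a fixed slope.

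A rank test is a defensible choice for a score with a maximum of 100, where a linear model may fit poorly. This was checked with scores rounded and capped at 0-100 (assumed means 55 and 70, SD 15). ANCOVA had power 0.95/0.91/0.88 against 0.78/0.78/0.79 for the planned test at rho 0.3/0.5/0.7, with null rejection of 4.4-4.7%. With the week-12 SD 1.3 times the baseline SD and the same cap, it was 0.87/0.84/0.81 against 0.75/0.76/0.77. The ceiling did not favour the rank test in these settings, though other shapes are possible.

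A reader might also infer that no effect estimate will be reported. That goes too far: the Statistical Analysis section plans means, SDs and CIs in general terms, and under a pure location shift the rank test is a valid test of d = 0. What stands is narrower: the article ties no estimate in VISA-A points to the primary comparison.

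Finally, 66 of 72 participants were randomized by October 2022. Changing a confirmatory test at that stage is a substantive amendment, and its timing relative to unblinding must be documented.

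**Conclusion.** The planned analysis is valid and meets its stated power. The weakness is one of efficiency and of sensitivity to chance baseline imbalance. It does not bias the test over repeated randomizations and does not undermine the sample size. ANCOVA had at least as much power as the planned test in every scenario examined, about 0.83-0.95 against about 0.80 with normal data. The variance reduction from adjustment runs from 0% to 35% over the assumed rho of 0.3-0.7 and SD ratios of 0.7-1, and is 5-10% for rho 0.9-0.8 with equal SDs. No single figure in that range can be claimed from the article. The direction is firm, because the large-sample variance difference (k − rho)² cannot be negative. The size is not firm. This is a worthwhile improvement, not the correction of a mistake.

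**What to change.** Before unblinding, in a dated amendment and in the SAP:

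- Make the primary analysis an ANCOVA of week-12 VISA-A on arm, with baseline VISA-A and the stratification factor site as covariates.
- Report the adjusted between-arm difference in VISA-A points with its 95% CI.
- Keep the planned Wilcoxon-Mann-Whitney test on change as a prespecified sensitivity analysis.
- Reword the hypotheses so that they refer to the adjusted mean difference.

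The sample size stays as it is, and no extra data or visits are needed. Statistically the cost is one degree of freedom for baseline plus those for site. The article does not give the number of sites, so the SAP should say how small sites are pooled. Procedurally the cost is an amendment to a confirmatory analysis late in recruitment. The article has the SAP being prepared in a blinded review, which is the natural place for the change. If unblinding has already taken place, the planned test must remain primary and the adjusted analysis can only be supportive.

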### Ethics Approval

The first positive ethics vote was issued on March 27, 2020, by the North Rhine Medical Association (reference No. U1111-1233-2760). Based on this, further positive ethics votes were subsequently issued for the other federal states in Germany where patients are recruited. Informed consent will be given before enrollment. This trial will be conducted in accordance with the ethical guidelines of the Declaration of Helsinki.

## Results

Onboarding of trial sites started at the end of 2020. Enrollment of the first participant occurred on May 28, 2021. As of October 2022, we randomized 66 out of 72 participants. We anticipate completing recruitment by the end of 2022 and completing primary data analysis by March 2023.

## Discussion

### Overview

Evidence-based therapies for AT are rare, leaving practitioners and patients with limited treatment options [21]. Against this background, PBCS has the potential to become one of the few effective therapies available. Therefore, this clinical trial will compare the therapeutic effects of verum versus control PBCS on AT. We aim to show that PBCS could improve function, pain, and other clinical outcomes by measuring differences between VISA-A, NRS, and PDI scores. Although many cases of AT can heal spontaneously, chronic courses, where the symptoms persist for months or years, are frequent. There is no clear evidence on whether AT that includes partial tendon rupture needs to be treated surgically [15]. Surgical treatment of acute Achilles tendon ruptures has been shown to reduce the risk of rerupture compared with nonoperative treatment. However, rerupture rates were low, and differences between treatment groups were small [15,22]. Surgery and injections are associated with various risks, mostly attributable to increased risk of infection [23,24]. Limited therapeutic options for treating AT result in a significant medical need for research and development of effective conservative treatments. With the PBCS treatment, we aim to advance nonsurgical treatment options for practitioners. Up to now, there have been no other comparable randomized controlled trial studies available on microinvasive direct current stimulation for the treatment of AT.

Unlike electroacupuncture or TENS therapy, the PBCS stimulation current is so low—in the range of a few microamperes instead of milliamperes—that it cannot be perceived by the patient. Consequently, the patient cannot reliably distinguish between a verum and a placebo stimulation. This makes it possible, unlike with TENS and electroacupuncture, to actually blind the verum and placebo electrostimulation to the patient and the therapist. In addition, the success of the blinding is checked by a blinding question within the study.

### Limitations

Insertion of needle electrodes is mandatory for the application of PBCS. Prior studies have shown that no placebo control for needle insertion is available and that needling itself can have clinical effects [25]. For this reason, therapeutic effects of needling may influence the results independently of the study intervention. In the verum and placebo groups, needle electrodes are positioned and inserted in an identical manner. The practitioner locates the particularly pain-sensitive points in the area of the Achilles tendon and advances the needle to the painful point. This procedure corresponds to dry needling or professional acupuncture at locus dolendi points; it has been shown that this kind of needling can produce therapeutic effects in pain disorders [26,27]. Therefore, the mere insertion of the needle probes, independent of electrical stimulation, may raise the success rate in both verum and control groups. In light of this consideration, we will additionally examine whether the therapeutic effect of electrical PBCS exceeds that of pure needle insertion. We are convinced that this will further strengthen the clinical relevance of the study.

### Conclusion

This study will evaluate the effects of PBCS on pain, physical function, and clinical outcomes in AT patients. Given the refractory nature and limited therapeutic options for AT, we aim to advance evidence-based nonsurgical care for patients and practitioners.

## Appendix

Multimedia Appendix 1 CONSORT-eHEALTH checklist (V 1.6.1).

## Abbreviations

AE: adverse event
AR: adverse reaction
AT: Achilles tendinopathy
EDC: electronic data capture
ITT: intention-to-treat
NRS: Numeric Rating Scale
NSAID: nonsteroidal anti-inflammatory drug
OEM: original equipment manufacturer
PBCS: percutaneous bioelectric current stimulation
PDI: Pain Disability Index
SAE: serious adverse event
SAR: serious adverse reaction
TENS: transcutaneous electrical nerve stimulation
VISA: Victorian Institute of Sports Assessment
VISA-A: Victorian Institute of Sports Assessment–Achilles questionnaire
VISA-A-G: German adaptation of the Victorian Institute of Sports Assessment–Achilles questionnaire
